### Data collection

Data will be collected at baseline (T1), and then after 12 weeks (T2) and 24 weeks (T3). Table 2 below outlines the information collected at the different time points. The visit will take place at a time and place convenient to the foster carer, either at the foster carer’s home or at an HPFT site, and is estimated to take up to 2 h.

**Table 2 Tab2:**
[figure not shown]
Schedule of Assessments

Table 2 shows the schedule of assessments. During the baseline assessment, after informed consent has been obtained, the participants will provide fuller information about their demographic status and history as outlined in the CRF. This basic data set will be followed by completion of the baseline outcome assessments.

### Treatment phase (0–12 weeks)

As part of routine practice, the therapist agrees with the child and the carer the goal(s) (usually up to three) for the therapy and goals are reviewed periodically throughout the therapy sessions. These goals are written down and recorded on a Goal-Based Outcome Measure (GBOM) Record Sheet.

The therapist will complete the Treatment Attendance Form over the period of therapy (0–12 weeks) for all participants, for all therapies (MBT and UCC). This includes details of the type of therapy utilised within the session (e.g. play therapy, CBT, and MBT). If the participant did not attend their scheduled therapy session, this will also be recorded with a reason, where possible.

In order to monitor adherence to the MBT model and differentiation from UCC, if the participant has consented to sessions being recorded, the therapist will audio-record each treatment session. At the end of the study, recordings for two of the families for each clinician in both arms of the study, selected randomly, will be reviewed by independent raters using an adaption of the MBT Competence and Adherence Scale to establish both treatment integrity and treatment differentiation.

### Follow up research visits

The T2 visit will occur at 12 weeks post-randomisation, which may or may not be after therapy has been completed. At 24 weeks from randomisation (T3), the final follow-up visit will take place. These assessments will consist of the outcome assessments completed at the baseline visit, plus the GBOM Scoring Sheet, the Experience of Service questionnaire, and record any significant events that may have occurred in the preceding weeks since the last assessments. In addition to the T2 measures, the T3 visit will also include a semi-structured interview in-person with the carer (and the child, where appropriate) about their experience of therapy and the research process. With consent, the interview will be audio-recorded. The interview will take place after all other assessment measures have been completed.

### Trial governance

The chief investigator (CI) will be accountable to the sponsor (the Anna Freud National Centre for Children and Families-AFNCCF) and will hold overall responsibility for the trial, including submission of required progress reports to the NIHR and NHS ethics committee, deliverables, financial statements and the correct use of funds.

The core study management team will consist of [name], [name] and [name], who together will take responsibility for monitoring the overall progress of the study, including both data and budget management, and supervising the RF(s). The TM will manage the day-to-day running of the study with the support of the Clinical Trials Support Network.The CTSN will provide data-management and on-going data monitoring, including randomisation procedures, setup of the online database and secure management of confidential participant data. Co-investigators who will provide support to the study in relation to their specific areas of expertise. A study steering committee (SSC) has been set up to monitor progress and advise, meeting five times (0, 6, 12, 18, and 24 months), and will be responsible for monitoring patient safety.

### Planned analysis

The purpose of the statistical and qualitative analysis is to evaluate the feasibility of undertaking a full clinical trial. The strategy employed is therefore to describe aspects of the data following the six aims outlined above; the approach to each aim is described in turn.

### Aim 1: evaluation of treatment integrity

The primary data considered will for the first aim be the MBT Adherence and Competence Scale. The data for each MBT therapist (*N* = 3) will be tabulated to determine whether the therapists are consistently achieving at least an “adequate” rating on the target therapeutic qualities on the scale. Should any of the therapists not achieve the target set, the qualitative data will be evaluated to determine the extent to which the reasons could potentially compromise a training regimen for therapists. The data for each UCC therapist (*N* = 3) will be tabulated to determine whether there is a statistically significant difference between them and the MBT therapists in the level of mentalizing techniques used in sessions, i.e. to establish whether there is differentiation between the two treatment arms.

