### Randomisation method and blinding

Individual participant randomisation will be utilised for the duration of the study with children assigned to one of the two treatment arms (MBT or UCC). Randomisation will be managed by the Clinical Trials Support Network (CTSN) at the University of Hertfordshire (UH), and will be requested and actioned electronically by the TM via the online secure data management system. Randomisation will be stratified by age (5–11 and 12–16), sex and whether the participant has siblings who are eligible, and otherwise randomly allocated. Randomisation will occur as soon as possible after consent has been obtained and the baseline assessment completed.

Six therapists are engaged in the study, and were placed into three pairs based on experience, ranging from senior to newly qualified social workers. The therapists were then randomly allocated to a treatment arm within each pair (one to each arm).

It is not possible to blind the therapists to treatment allocation, and for pragmatic reasons a decision has been made not to blind the child and foster family. Blinding of the child and foster family is judged not to be desirable (to avoid the perception of manipulation by the study team), and would be difficult to achieve, given that the MBT intervention involves active collaboration around the use of a mentalizing approach.

The members of the research team collecting and coding the research data and the study statistician will be the only team members blinded to treatment allocation; therefore, randomisation code breaking will not be necessary during the study.

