### Sample size determination and power

The sample size of 42 is primarily calculated to test consistency with desired primary outcome effect size. Following Cocks and Torgerson [45], a sample size sufficient to reject a lower limit for the effect size of 0 is estimated (assuming one sided *α* = 0.05, 1− *β* = .80). Assuming sd = 7 in the SDQ is representative, with a lower limit = 2 for meaningful clinical change, the effect size = .29. For a feasibility trial, to reject an effect size of 0 a sample size of 32 (16 in each arm) is required, or 42 children (21 per arm) allowing for 30% drop out.

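### Aim 1 judges differentiation between the arms by statistical significance with three therapists per arm, so a non-significant result could not show that the arms were undifferentiated

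*Protocol article*

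**What the plan says.** The Aim 1 section of the protocol article sets out two tabulations. For the intervention arm, "The data for each MBT therapist (*N* = 3) will be tabulated" to see whether each therapist consistently reaches at least an adequate rating. For the control arm, "The data for each UCC therapist (*N* = 3) will be tabulated", and here the question is "whether there is a statistically significant difference between them and the MBT therapists in the level of mentalizing techniques used in sessions". The stated purpose of that comparison is "to establish whether there is differentiation between the two treatment arms".

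Two other sections fix the structure of the data. Under Randomisation method and blinding, six therapists were placed in three pairs by experience: "The therapists were then randomly allocated to a treatment arm within each pair (one to each arm"). Under Treatment phase (0–12 weeks), "recordings for two of the families for each clinician in both arms of the study, selected randomly, will be reviewed by independent raters". Each therapist therefore contributes two rated families, and the number of rated sessions per family is not given.

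Aim 1 names no test, significance level or sidedness. The Planned analysis section describes the general approach as descriptive: "The strategy employed is therefore to describe aspects of the data following the six aims outlined above".

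**The concern.** The therapist is the unit that was allocated to an arm, and the text itself labels the comparison N = 3 against N = 3. With so few units, a significance test says little unless the gap is very large. The likely error is to read a non-significant result as failure to differentiate MBT from usual care when the two sets of therapists in fact worked quite differently.

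This matters because all six clinicians belong to one team. The Interventions section names contamination as a risk and relies on separate supervision to limit it. The rated recordings are the quantitative evidence on whether that worked. A misreading would misinform the judgement on how the treatments could be kept apart in a full trial.

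There is an opposite risk if the small number is met by counting several ratings from one therapist as independent observations. Ratings from the same therapist are likely to be alike, and the test would then reject too often.

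**Working it through.** The protocol gives no power or detectable difference for this comparison, so there is no figure to reproduce.

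**Inputs from the protocol**
- 3 MBT and 3 UCC therapists (Aim 1).
- Three matched pairs, one therapist to each arm (Randomisation method and blinding).
- Two rated families per clinician (Treatment phase).

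**Assumptions**
- Two-sided 5% as the main case, with one-sided 5% alongside. The only alpha in the protocol is in the sample size section for the SDQ ("assuming one sided *α* = 0.05").
- 80% power as the benchmark, which the protocol also gives only for the SDQ.
- SD means the between-therapist SD of therapist-level scores. The protocol gives no value for it.

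**1. Exact tests at complete separation**
- Unpaired: there are C(6,3) = 20 ways to split six therapists three and three. Smallest two-sided p = 2/20 = 0.10; one-sided 1/20 = 0.05.
- Paired (sign-flip over three pairs): 2³ = 8 arrangements. Smallest two-sided p = 2/8 = 0.25; one-sided 1/8 = 0.125.

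**2. Two-sample t-test on therapist means, df = 4**

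Smallest significant observed gap = t × √(2/3) SD. Power comes from the noncentral t with noncentrality d × √(3/2).

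| | Two-sided 5% | One-sided 5% |
|---|---|---|
| Critical t | 2.776 | 2.132 |
| Observed gap needed | 2.776 × 0.8165 = 2.27 SD | 2.132 × 0.8165 = 1.74 SD |
| True gap for 80% power | 3.07 SD | 2.48 SD |
| Power at a true gap of 2 SD | 46% | 65% |

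At two-sided 5%, power is 16% at a true gap of 1 SD and 78% at 3 SD. A paired t-test (df = 2) needs an observed mean difference of 4.303/√3 = 2.48 SD of the pair differences, and a true one of 3.26 for 80% power.

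**3. If ratings within a therapist were treated as independent**

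With m ratings per therapist and within-therapist correlation ICC, the design effect is DE = 1 + (m − 1) × ICC. A nominal two-sided 5% test then has a type I error of about P(|Z| > 1.96/√DE). Both the ICC and m = 8 are assumed; m = 2 corresponds to one rating for each of the two families.

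| ICC (assumed) | m = 2: DE, type I error | m = 8: DE, type I error |
|---|---|---|
| 0.1 | 1.1, 6% | 1.7, 13% |
| 0.3 | 1.3, 9% | 3.1, 27% |
| 0.5 | 1.5, 11% | 4.5, 36% |

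Simulating the t-test on 6 against 6 families gave 6%, 9% and 12% for the m = 2 column, in line with the approximation. In the same simulation, testing the therapist means held the error at about 5%, but with 4 df, which leads back to step 2.

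**The case against.** The strongest reply is that Aim 1 fixes neither the test nor its level, that such detail is commonly left to an analysis plan, and that the expected direction is obvious. One-sided, the unpaired exact test attains 0.05 at complete separation and the t-test has 65% power at 2 SD. The scale is specific to MBT, so a gap of several SD is plausible. The general strategy is descriptive, the therapist data are to be tabulated anyway, and the section on evaluating a full-scale trial ties no progression decision to this p-value.

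Much of this stands, and it limits the point. A reader might infer that significance is out of reach without pseudo-replication. It is not: a valid therapist-level t-test succeeds at an observed gap of 2.27 SD. Nor does the protocol say that sessions or families will be treated as independent, so the type I error figures describe a hazard and not a stated plan. A reader might also infer that the recordings will be rated with the arm known, but the protocol blinds the team members who code the research data and uses independent raters.

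What the reply does not remove is the choice of criterion. An analysis plan can name the test and its sidedness, but it cannot change three therapists per arm. Under any of the therapist-level tests above, a non-significant result remains compatible with a large difference.

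**Conclusion.** The point holds as a criticism of the criterion. With three therapists per arm, statistical significance is a poor way to decide whether the treatments were differentiated. At two-sided 5%, a true gap of 2 between-therapist SD would be missed slightly more often than found (46% power), and an exact test could not succeed at all. At one-sided 5% the position is better but still weak: complete separation is required for the unpaired exact test, and about 2.5 SD for 80% power with the t-test.

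The consequence is asymmetric. A significant therapist-level result would be informative; a non-significant one could not show lack of differentiation. The 2.27 SD and 3.07 SD figures rest on the assumed two-sided level and, for power, on normally distributed therapist scores. The inflation figures, about 6% to 11% with two ratings per therapist and 13% to 36% with eight, rest on assumed ICCs of 0.1 to 0.5 and apply only if clustering is ignored. The point concerns one of six feasibility aims. It does not touch the SDQ outcome or participant safety.

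**What to change.** In the Aim 1 section, remove statistical significance as the criterion for differentiation. In its place:

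- report the ratings for each of the six therapists, showing the experience pairs;
- report the MBT minus UCC difference in therapist means with a 95% CI that uses the therapist as the unit;
- judge differentiation on the size of that difference and on how far the therapist scores of the two arms overlap;
- state that a CI including zero is not evidence of no differentiation.

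The last item is needed because the unpaired interval has a half-width of 2.27 SD (the same 2.776 × √(2/3)) and excludes zero exactly when the two-sided t-test is significant. The gain comes from reading size and overlap, not from swapping a p-value for an interval.

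The cost is a change of wording. It needs no new recordings, raters or participants, and it fits the descriptive strategy in the Planned analysis section. The downside is that there is no p-value to quote and the interval will be wide.

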### Aim 2: feasibility of recruitment

The recruitment data will be presented in terms of absolute numbers and by proportions. In particular, the conversion of CLA referred to the CAMHS targeted team into children randomised to the study will be estimated as a key indicator of the feasibility of undertaking a full trial. The reasons for being excluded from the study at each point will be tabulated. The reasons for drop-out or exclusion will be examined for any consistent trends that may be addressed in the study design.

### Aim 3: acceptability of MBT as an intervention

For this aim, the primary data will be the extent to which children and carers attended therapeutic sessions as scheduled and the Experience of Service Questionnaire (CHI-ESQ-[30]). The analysis will tabulate therapeutic attendance, using both median and range data, and seek to determine particular trends where possible. It may be possible to evaluate the extent to which non-attendance is related to particular demographic or clinical factors crudely via regression models, or via stratification of the sample. Listing and classification of significant events during the children’s treatment may also help to highlight different effects on attendance patterns.

The acceptability of MBT as an intervention will also be assessed qualitatively, using the *Experience of Therapy and Research Process Interview.* A thematic analysis [43] will be conducted, to identify which elements of the intervention were experienced as acceptable or non-acceptable, and this will inform further development of the MBT intervention model if a full clinical trial is undertaken.

### Aim 4: feasibility and acceptability of randomisation & research procedures

The primary aim of this evaluation will be to examine data completion and retention across the study once the child has been randomised to a treatment arm. Data completion rates will be documented across all the outcome measures, and by treatment arm, and by time point. The analysis will seek to determine whether data completion falls below 75%, and potential differences between treatment arms, responding groups (children, families, teachers) and by subgroups (sex, age [≤11 or >11]), or any other demographic or clinical factor.

The study allows for a 30% drop out at the last follow-up [44]; and the data will be examined similarly for trends in the drop-out of children and their families. This will be tabulated according to treatment and subgroup as outlined above. Drop-out will be matched (tabulation) to the attendance data and to significant events to determine the extent to which drop out is determined by these factors. Regression models may be evaluated whether these factors are potentially informative and the study sample size allows.

The acceptability of randomisation, as well as other elements of the research design, will also be assessed qualitatively, using the *Experience of Therapy and Research Process Interview.* A thematic analysis [43] will be conducted to identify which elements of the research design were experienced as acceptable or non-acceptable. In addition to the process of randomisation, this will include the assessment burden and the appropriateness of each of the research measures (e.g. whether the parenting measures were felt to be appropriate for the experience of foster carers). This will inform the design if a full clinical trial is undertaken.

### Aim 5: resource use data

A similar approach to evaluating (non) completion of the resource use scales (CAS-US and CHU-9D) will be applied as for Aim 4. In addition, an evaluation of the meaningfulness of the data collected on the CA-SUS compared to the costs incurred by the children involved in the study will be undertaken. The extent to which the costs appropriately capture the financial challenge that the children present to the NHS and Social Care will be considered.

### Aim 6: likely effect size of the intervention

The preliminary effect size estimated for this study is based on an assumed minimum difference in the SDQ of 2 points given an sd = 7 typical of this sample of children. This gives a conservative estimate for an effect size of .29, and the sample size is estimated to enable a lower limit of 0 to be rejected. The analysis will seek to estimate the effect size from the observed data, with an estimated lower limit as suggested by Cocks and Torgerson [45].

### Evaluating the feasibility of a full scale trial

Principal determinants of whether a full scale trial can be undertaken will follow evaluation of each of the study aims as outlined.

Bringing together all the study data will allow trial feasibility to be considered, including the following:The potential to train therapists to deliver the intervention as envisaged and the costs involved.That the external validity of the study is maximised by ensuring that drop-out from the study is within acceptable limits (30%), or that changes can be convincingly made to the study procedures to allow for improved retention in the study.That the internal reliability of the study data is maintained. Data completion for the study measures, and completion of the therapeutic intervention (attendance) will be evaluated to ensure that the completion rate is good (>75%) and that there are no obvious biases in data completion by any particular subgroup. The qualitative evaluation will be considered in informing particular changes that can be made to maximise the study procedures to improve data completion.

The final report will summarise the data to support clear decision to proceed to a full trial, and to inform development of the study procedures to maximise the quality of the trial design.

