### The outcomes of the study

The key outcomes of the study relate to the feasibility of conducting a large-scale RCT. The specific feasibility outcomes are as follows, with details of the instruments, scales, assessments and interviews to be utilised:The capacity to train mental health practitioners (treatment integrity):The *MBT Adherence and Competence Scale* [29], rating both adherence and competence.Therapist feedback forms, to provide qualitative feedback about the MBT training and experience of its use in practice.
The feasibility of the recruitment processes:A *Recruitment Log*, including number of children referred, meeting inclusion/exclusion criteria, completing baseline assessment, randomised into the trial and reasons for non-eligibility or non-participation. This data will help to determine how long it would take to recruit participants into a definitive trial and the necessary referral levels/number of services that should be involved.
The acceptability and credibility of MBT as a treatment intervention for CLA:A *treatment attendance form*, recording non-attendance, and withdrawal with reasons. UCC group includes details about planned/received treatment.The *Experience of Service Questionnaire* (CHI-ESQ; [30]) in child, adolescent and carer formats, assessing service satisfaction.The *Experience of Therapy and the Research Process Interview* [31]; a qualitative interview with foster carer (and child, where appropriate) examining the experience and acceptability of the intervention.
The feasibility and acceptability to families of conducting a randomised clinical trial:The *Experience of Therapy and the Research Process Interview* [31] includes the family’s experience of, and barriers to participation in the trial. This qualitative data, along with data from the Case Report Form (CRF), will be used to assess feasibility and acceptability of the trial procedures themselves. This would include (a) the process of consent and randomisation and (b) the response rates for primary and secondary outcome measures, including retention at each of the three data collection time points and level(s) of missing data.
The feasibility of collecting resource-use data:
*Child and Adolescent Service Use Schedule* (CA-SUS: [32]; assessing resource use.
*Child Health Utility 9D* (CHU9D: [33]); assessing health-related quality of life.

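### The >75% data-completion limit has no stated denominator, so its fit with the 30% drop-out limit is unclear, and the drop-out limit accepts fewer children than the sample size requires

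*Protocol article*

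**What the plan says.** The protocol article gives two numeric limits under 'Evaluating the feasibility of a full scale trial'.

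- **Drop-out**, linked there to external validity: "ensuring that drop-out from the study is within acceptable limits (30"%). An alternative follows at once: "or that changes can be convincingly made to the study procedures to allow for improved retention in the study".
- **Completion**, linked to internal reliability. Completion of the study measures, and of the therapy itself, "will be evaluated to ensure that the completion rate is good (>75"%).

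The Aim 4 section places the first limit in time: "The study allows for a 30% drop out at the last follow-up". On the second it says: "The analysis will seek to determine whether data completion falls below 75"%. It sets the level of reporting as follows: "Data completion rates will be documented across all the outcome measures, and by treatment arm, and by time point". It introduces the whole evaluation as one that will "examine data completion and retention across the study once the child has been randomised to a treatment arm".

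'The outcomes of the study' describes response rates for the outcome measures as "including retention at each of the three data collection time points and level(s) of missing data".

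'Sample size determination and power' requires 32 children (16 per arm) and raises this to 42 (21 per arm) for 30% drop-out.

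None of these sections states the denominator of the completion rate, or whether 75% must be reached at each visit or overall.

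**The concern.** Drop-out and data completion overlap at the final visit, because a child who has left the study has no 24-week data. Whether that child counts against completion depends on the denominator. If so, the completion limit is the stricter of the two at 24 weeks and the 30% allowance has no practical effect there. If not, the completion limit says nothing about children who left, and the two limits together tolerate much more missing outcome data than either figure suggests.

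The final report is meant to support a clear decision on a full trial. With drop-out between 25% and 30%, close to what the plan itself allows for, the same data could be described as meeting both limits or only one. The retention limit also needs to agree with the number of children the sample size section says must be analysable, and it does not.

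**Working it through.** **Inputs.** Randomised N = 42 and required n = 32, with a 30% drop-out allowance (sample size section). Drop-out limit 30%, placed at the last follow-up, 24 weeks (progression section and Aim 4). Completion limit above 75% (progression section).

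**The plan's own figure.** 32 × 1.30 = 41.6, rounded up to 42. So 42 is reproduced by adding 30% to 32. Taking 30% away from 42 gives 42 × 0.70 = 29.4, which is below 32. Dividing instead, 32 / 0.70 = 45.7, or 46.

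**Drop-outs that pass the 30% limit.** 0.30 × 42 = 12.6, so up to 12 pass, leaving 30 retained.

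**Reading A: completion over all randomised children at 24 weeks.** The highest possible completion is (42 − drop-outs) / 42. Exceeding 75% takes more than 0.75 × 42 = 31.5 children, so at least 32.

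| Drop-outs | Drop-out | Retained | Maximum completion | Within 30%? | Can exceed 75%? |
|---|---|---|---|---|---|
| 10 | 23.8% | 32 | 76.2% | yes | yes, if all 32 have data |
| 11 | 26.2% | 31 | 73.8% | yes | no |
| 12 | 28.6% | 30 | 71.4% | yes | no |
| 13 | 31.0% | 29 | 69.0% | no | no |

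The limits diverge at 11 and 12 drop-outs. With 10 or fewer, both can be met.

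**How likely are 11 or 12 drop-outs?** Binomial probability of exactly 30 or 31 retained out of 42, by assumed true retention:

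| True retention | 70% | 72% | 75% | 80% | 85% | 90% |
|---|---|---|---|---|---|---|
| Probability | 0.252 | 0.269 | 0.254 | 0.143 | 0.035 | 0.002 |

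It is about one in four if retention is near the planned level and small if retention is good. It matters only under Reading A.

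**Reading B: completion over children still in the study.** With 12 drop-outs, 30 remain. More than 75% of 30 is more than 22.5, so 23 is enough (23 / 30 = 76.7%). Both limits are then met with 24-week data on 23 / 42 = 54.8% of those randomised.

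**Reading C: pooled over the three visits.** With 12 drop-outs and all forms otherwise complete, completion is (42 + 30 + 30) / 126 = 81.0% if all are lost before week 12, and (42 + 42 + 30) / 126 = 90.5% if all are lost after it. There is no conflict, but complete baseline data mask the loss at 24 weeks. Reporting by time point in Aim 4 points away from this reading.

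**Against the sample size, on any reading.** The drop-out limit accepts 30 retained. The required number is 32, and 32 / 42 = 76.2%, so a retention limit that protects 32 lies just above 75%, not at 70%.

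**The case against.** A reader might infer that the two limits contradict each other, or that more than 75% completion is impossible at 24 weeks. The document does not support that, for three reasons.

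- The conflict needs a denominator that is never given. The reference to the child having been randomised can be read as naming the stage of the study that Aim 4 covers. Drop-out and completion are handled in separate paragraphs and tied to different kinds of validity, so completion among those still in the study is a fair reading.
- Even over all randomised children, both limits can be met with 10 or fewer drop-outs. One limit is then merely stricter at one visit.
- Neither limit is a hard stop. The drop-out limit has the stated alternative of convincing changes to procedures, and qualitative findings are to inform changes that improve completion.

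All three stand. A reader might also infer that age-restricted questionnaires would fail the limit simply because younger children do not receive them. The outcomes section already confines each questionnaire to its age range, so that does not follow.

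A further defence is that a journal article may leave a denominator to the full protocol or analysis plan, and that completion and drop-out will both be tabulated. This has some force, and there is no basis for saying that the denominator would be picked after the data are seen. It does not settle the matter. The article itself sets the numeric limits, and its account of response rates as including retention makes the all-randomised reading a well-supported one. The shortfall against 32 children does not depend on the denominator at all.

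**Conclusion.** The point holds as a modest correction to how the progression limits are fixed. The completion denominator is not stated, and the choice changes what the limit means. Over all randomised children at 24 weeks, 11 or 12 drop-outs of 42 pass one limit and cannot meet the other. Over children still in the study, the limits are compatible but accept 24-week data on as few as 23 of 42 (55%). Separately, and on either reading, the 30% limit accepts 30 retained where the sample size section requires 32.

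This assumes that exactly 42 are randomised, that a child who drops out contributes no 24-week data, and that the required 32 is taken as stated.

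**What to change.** Amend the wording of the Aim 4 and progression sections to give two rules with fixed denominators.

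1. **Retention.** The share of all randomised children with a carer-rated SDQ at 24 weeks, with one limit. Set it above 75% if 42 randomised must deliver 32. Alternatively keep 70%, and restate the expected evaluable number in the sample size section as about 29 (0.70 × 42 = 29.4).
2. **Form completion.** More than 75% for each measure, at each visit, among families retained at that visit whose child is in the measure's age range.

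Report both with 95% confidence intervals, since a proportion out of 42 is imprecise. Keep the existing provision that procedural changes may answer a shortfall. The cost is a few sentences. No new data, visits or participants are needed.
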